### System-wide electronic surveillance

Electronic medical records (EMR) facilitate early recognition of specific study criteria using Boolean combinations of clinical variables and natural language processing. In this study we are planning to use a customized, integrative relational research database that contains a near-real time (15 minutes delay) copy of electronic medical records (ICU DataMart). To identify Olmsted County residents at risk admitted to the two Mayo Clinic hospitals, ICU DataMart uses 9-digit ZIP code and a specific nursing unit codes and generates e-mail and/or pager alert within 15 minutes from the time the patient is assigned a bed in the receiving unit. Patients admitted for labor and delivery, specific procedures (cardiac catheterization), cardiac telemetry, coronary care unit, low risk elective surgeries and children are excluded from the alerts. Screening for ALI development is performed by previously validated ARDS "sniffer" [20,21]. The electronic alert is triggered by the following combination of observations: 1) qualifying arterial blood gas analysis: the ratio of partial pressure of oxygen to inspired oxygen concentration (PaO_2_/FIO_2_) <300 and 2) qualifying chest radiograph report: free text Boolean query containing trigger words: ("bilateral" AND "infiltrate") OR "edema" The ARDS sniffer demonstrated excellent negative predictive value (0.99, 95% CI 0.98 to 1.00)[20]. ARDS-sniffer has been continuously running since December of 2005 allowing for prospective identification of ALI cases. Access to the database is accomplished through password protected open database connectivity (ODBC) using JMP and SAS statistical software (SAS Institute Inc., Cary, NC, USA).

### Early identification of patients at risk of ALI (lung injury prediction score - LIPS)

To facilitate enrollment of patients into mechanistic and outcome studies as well as future ALI prevention trials, we have recently developed an ALI prediction model (Lung Injury Prediction Score: LIPS, Table 1)[22]. LIPS incorporates demographic, and clinical characteristics at the time of, and before, hospital admission. Risk factors for ALI that were identified in at least two previous studies were used in model development. LIPS points were determined based on parameter estimates from the logistic regression model, taking into consideration results from our previous studies. The model accurately discriminated between the patients who did and did not develop ALI with an area under the receiver operating curve of 0.85 (95% CI 0.80 to 0.89) [22].

Twice daily (7 AM and 5 PM, Monday-Saturday) trained study coordinators review syndrome surveillance alerts of new Olmsted County admissions and apply LIPS points to patients who fulfill the inclusion criteria according to LIPS score sheet. ODBC MS Access database tool is used for the collection of individual patient data in a systematic way. The database automatically links MS Access to ICU Datamart server and imports new patients from ICU Datamart to the LIPS database. The database also links automatically to the IRB research authorization web site identifying the patients that have approved the use of their medical data for research.

### Validation of the primary outcome (ALI)

Primary outcome is the development of ALI at any time during the hospital stay. Trained investigators review each ARDS sniffer alert (see above) and confirm the presence or absence of ALI according to the standard definition based on the American-European consensus conference [21]. The absence of left atrial hypertension as the principal explanation for pulmonary edema is confirmed by integrated clinical evaluation based on the following:

• Echocardiography (E/E'<15, EF>45)

• Pulmonary artery occlusion pressure (PAOP) ≤ 18 cm H2O

• Central venous pressure (CVP < 15) cm H2O (higher cutoff in pulmonary hypertension)

• History of congestive heart failure/cardiogenic pulmonary edema

• Brain natriuretic peptide (BNP) <250 pg/mL (higher cutoff in renal failure)

• Response to preload reduction: brisk (hours) response to diuretics and/or positive pressure ventilation favors hydrostatic edema

This process yielded good interobserver agreement for differentiation between ALI and hydrostatic edema (Kappa value 0.83 in the most recent retrospective Olmsted county study)[10].

### Identification of in-hospital exposures

To identify candidate interventions for ALI prevention, we are planning to identify hospital acquired (2^nd ^hit) environmental exposures that may modify the risk of ALI and its consequences in high risk subgroups of patients residing in the Olmsted County community identified by the LIPS model. Timing and intensity of environmental exposures (Table 3) will be determined by the review of monitoring logs, nursing and physician interventions in the EMR by trained study coordinators blinded to ALI status. Only the exposures occurring before development of the ALI in cases and during the corresponding period of time in controls will be analyzed as modifiers of ALI development.

**Table 3 T3:** Hospital (second hit) exposures that may modify the development of ALI in high risk patients.

	Variable	Measurements

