**A. Exposures associated with development of ALI in preliminary studies**		
Treatment of infection	Antibiotics	Time to administration of adequate antibiotics
	Source control	List source, time to source control
Shock resuscitation	Early goal directed resuscitation	Time to completion of goal directed resuscitation
Blood transfusion	Red blood cells, fresh frozen plasma, platelets	Number of units, donor gender and pregnancies, storage age of red cells and platelets
	
Respiratory support	Inspired oxygen concentration (FIO_2_)	AUC, mean, median and maximum value during the exposure time of interest
	
	Ventilator tidal volumes (mL/kg predicted weight)	AUC, mean, median and maximum value during the exposure time of interest
	Peak and plateau airway pressures (cm H_2_O)	AUC, mean, median and maximum value during the exposure time of interest
	PEEP (cm H_2_O)	5-10 (reference), <5, >10 cm H_2_O
	
	Respiratory rate	AUC, mean, median and maximum value during the exposure time of interest
Medications	Amiodarone	Cumulative dose during the exposure time of interest
	Chemotherapy	Cumulative dose during the exposure time of interest
Other complications	Aspiration (in hospital)	Inhalation of food or gastric contents
	Medical or surgical misadventures	List complication (ICD-9 code E870-E879.9)

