### Statistical Analysis

An estimate for the probability of ALI development will be calculated for each patient based on the LIPS model. Because of subjective nature of clinical definitions used to identify the outcome of our study, it is necessary to assess interobserver variability. Interobserver agreement for ALI development will be assessed by calculating the Kappa statistic, using a threshold of 0.6 as an indication of acceptable interobserver agreement.

The calibration and discrimination of model will be assessed using the Hosmer-Lemeshow goodness-of-fit test and the receiver operating characteristic curve, respectively. An area under the ROC curve greater than 80% will be considered to be the evidence of good model discrimination. Using a LIPS cutpoint of 3.5 or more identified in the preliminary data, the comparison of the model prediction versus the actual event observed will be summarized by a simple 2 by 2 table reporting ALI propensity versus ALI development. Summary measures, based on the 2 by 2 table, will be reported: sensitivity, specificity, positive predictive value, negative predictive value, positive and negative likelihood ratios along with their 95% confidence intervals.

In a matched case-control design the associations suggested by preliminary clinical studies (Table 3) will be compared between ALI cases and high risk controls propensity matched by age, gender and the probability of ALI development at the time of hospital admission (LIPS, see above). Subpopulation analyses will be performed to determine what hospital exposures are associated with ALI in low/moderate ALI risk patients and what hospital exposures factors are associated with no ALI development in high ALI risk patients. The primary statistical endpoint is the development of ALI at any time during hospital stay. The matching is based on ALI risk at admission and the exposure period at risk. For example, if a hospitalized patient, who has an estimated propensity for developing ALI of 20% actually develops ALI 10 hours after hospital admission the exposures in matched control patient is only measured during the initial 10 hours after hospital admission. Paired statistics will be used for group comparisons. A conditional logistic regression model will be built in the case of baseline imbalances.

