The principal limitation of our study is imposed by the broad nature and definition of the primary outcome of interest, ALI [21]. The exclusion of left atrial hypertension poses a particular challenge in the clinical assessment of ALI. In addition to using a standardized definition and extensive training of study personnel, all ALI cases will be reviewed by trained expert investigators. There is a possibility of ascertainment bias as we will depend on the clinicians caring for the patient to order the chest x-ray and the arterial blood gas necessary to diagnose ALI. Fortunately, almost all patients requiring respiratory support do have these tests performed routinely every day. It is therefore extremely unlikely that a significant ALI would occur without the need to perform the chest x-ray and the arterial blood gas as a part of clinical care.

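### Exposures are counted up to ALI onset with no lag, so escalation prompted by evolving, not yet recorded ALI can look like a cause for exposures that respond to respiratory decline

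*Protocol article*

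**What the plan says.** Under Identification of in-hospital exposures, the protocol article states: "Only the exposures occurring before development of the ALI in cases and during the corresponding period of time in controls will be analyzed". Statistical Analysis gives an example. If a case develops ALI 10 hours after admission, "the exposures in matched control patient is only measured during the initial 10 hours after hospital admission". The hours just before onset are therefore kept in the case, and the same hours in the control.

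Under System-wide electronic surveillance, one of the two alert criteria is "the ratio of partial pressure of oxygen to inspired oxygen concentration (PaO_2_/FIO_2_) <300". The other is a qualifying radiograph report. Investigators then review each alert and confirm or reject ALI (Validation of the primary outcome).

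Table 3, part A, lists FIO2, tidal volume, airway pressures and respiratory rate as exposures, each summarised as "AUC, mean, median and maximum value during the exposure time of interest". PEEP is categorised. Furosemide, beta agonists and sedatives are cumulative doses in the exploratory part B.

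On detection, the Discussion says that "we will depend on the clinicians caring for the patient to order the chest x-ray and the arterial blood gas necessary to diagnose ALI", and that "almost all patients requiring respiratory support do have these tests performed routinely every day".

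**The concern.** By the article's own Background, ALI develops over hours to days. A period of deterioration can therefore precede recorded onset and fall inside the exposure window. During that period staff may raise inspired oxygen, change ventilator settings, or give diuretics, bronchodilators or sedation because the lungs are already failing. A window that runs to onset counts these responses as exposures that came before ALI. The matched control has a window of equal length, but no impending ALI at the end of it.

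FIO2 is the sharpest case, because it enters the screening ratio for the outcome and is also a candidate cause. The study means to identify candidate interventions for prevention and to inform later trials. A spurious association in one of these variables could be carried forward as a target.

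**Working it through.** The plan gives no figure on this point, so there is none to reproduce. The check has three parts.

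**1. Do the stated safeguards remove the problem?**

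- *Equal window length* (Statistical Analysis) equalises time at risk, not closeness to deterioration.
- *Matching on LIPS* (Table 1, Statistical Analysis) includes FIO2 above 0.35 and respiratory rate above 30, but only the worst values of the first 6 hours. Later escalation is unmatched.
- *Exclusion of ALI or pulmonary edema at admission* (Table 2) removes established disease, not disease that evolves afterwards.
- *Abstraction blinded to ALI status* prevents biased recording. It does not remove escalation that really happened.
- *Conditional logistic regression* is planned for baseline imbalances. The Discussion adds adjustment for measured predictors of each exposure. Neither is aimed at responses to the onset of the outcome itself.

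The safeguards are partial.

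**2. How much escalation would matter?**

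Inputs: 500 cases and 500 controls and a target odds ratio of 2.0 (Sample size considerations); false positive rate 0.05 (Figure 3 legend), taken as two-sided. Control prevalences p0 of 5% and 10% appear in Figure 3; 20% is an assumption. The share f of otherwise unexposed cases who become exposed only as a response to evolving ALI is an assumption throughout. The true odds ratio is set to 1.

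Case exposure: p1 = p0 + f(1 − p0). Apparent OR = p1(1 − p0) / [p0(1 − p1)].

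Setting the apparent OR to 2 gives p1 = 2p0/(1 + p0) and f = p0/(1 + p0):

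| p0 | p1 | f needed for OR 2.0 | Extra exposed cases, (p1 − p0) × 500 |
|---|---|---|---|
| 5% | 0.10/1.05 = 9.5% | 0.05/1.05 = 4.8% | about 23 |
| 10% | 0.20/1.10 = 18.2% | 0.10/1.10 = 9.1% | about 41 |
| 20% | 0.40/1.20 = 33.3% | 0.20/1.20 = 16.7% | about 67 |

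With f fixed, the apparent OR and the chance of a significant result (unmatched two-proportion approximation) are:

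| p0 | f = 5% | f = 10% |
|---|---|---|
| 5% | 2.05, 82% | 3.22, 99.9% |
| 10% | 1.53, 58% | 2.11, 98% |
| 20% | 1.26, 33% | 1.56, 84% |

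**3. Which summary is most exposed?**

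Assume FIO2 is 0.30 for 8 hours of a 10-hour window and is raised to 0.60 for the last 2 as a response:

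- mean: (8 × 0.30 + 2 × 0.60)/10 = 0.36, against 0.30 without the rise
- AUC: 3.6, against 3.0
- median: still 0.30
- maximum: 0.60, against 0.30

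The maximum takes the whole of the late rise; the mean takes a fifth of it.

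**The case against.** The strongest reply is that the article already confines exposures to the time before ALI and truncates each control's window to match. How onset is dated is detail that a condensed article may leave to the full protocol. That stands for the dating of onset: the article describes an alert trigger and an expert confirmation, and a reader should not infer that onset is simply the time of the alert. It does not answer the lag, because the article fixes the window and illustrates it with no gap.

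The Discussion also says tests are routine in patients on respiratory support, so one should not assume that they are ordered only on deterioration. This is fair. Roughly daily testing could still date onset up to about a day late, which is an inference.

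Three stronger readings are tempting and not supported:

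- *That the bias is certain, or always away from the null.* The share of escalated cases is unknown. For a response drug that truly protects, the same mechanism moves the estimate toward the null or past it.
- *That the plan rests on the maximum.* It is one of four summaries, and does not apply to PEEP, furosemide, beta agonists or sedatives.
- *That these are the likeliest prevention targets.* The targets named in the Discussion include high tidal volume, delayed treatment and aspiration triggers. FIO2, airway pressures, PEEP and furosemide are not among them. FIO2 and mechanical ventilation are, however, named as common exposures in Sample size considerations.

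Finally, any lag is a choice with costs. In the article's 10-hour example, a 6-hour lag leaves only hours 0 to 4, inside the LIPS scoring period, and a 12-hour lag leaves nothing. A lag can also delete a genuine late second hit. This argues against replacing the primary window, not against a lagged analysis beside it.

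**Conclusion.** The concern holds for exposures that respond to respiratory decline. It does not extend to exposures fixed independently of the patient's course, such as donor gender. With the window run to onset, the planned comparison cannot separate a cause of ALI from a response to its early phase, and the stated safeguards narrow this only partly.

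The size is unknown. The illustration shows that an association as large as the study's own detection target could arise with no true effect if about 5% to 17% of otherwise unexposed cases were escalated, for control prevalence of 5% to 20%. It treats exposure as yes or no. FIO2, pressures and respiratory rate are summarised as continuous values, so these odds ratios do not transfer to them directly. The 5% prevalence is attached in Figure 3 to delayed fluid resuscitation, not to respiratory support. The figures show that the problem could matter, not that it will.

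**What to change.** Keep the stated window, and add the following for FIO2, airway pressures, PEEP, respiratory rate, furosemide, beta agonists and sedatives:

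1. State how the time of ALI onset is set once an alert has been confirmed.
2. Repeat the matched analysis with the window ended a fixed, prespecified lag before onset in the case and at the same elapsed hour in its control. Lags of 6 and 12 hours are examples; the documents give no basis for a particular value.
3. Report lagged and unlagged estimates in the same retained pairs, so that a change is not merely due to lost pairs.
4. Where several summaries are planned, rely on the time-weighted mean and treat the maximum as supportive.
5. Do not put forward as a prevention target an association in these variables that disappears under the lag. Report it as unresolved, since a true late effect could also vanish.

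The article describes near-real-time electronic records and plans to capture the timing of exposures, so the work is mainly programming. The costs are real: pairs with onset inside the lag drop out of these analyses, precision falls, and short lagged windows overlap the 6-hour LIPS period already used for matching, so FIO2 and respiratory rate may be overmatched there.

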**A. Exposures associated with development of ALI in preliminary studies**		
Treatment of infection	Antibiotics	Time to administration of adequate antibiotics
	Source control	List source, time to source control
Shock resuscitation	Early goal directed resuscitation	Time to completion of goal directed resuscitation
Blood transfusion	Red blood cells, fresh frozen plasma, platelets	Number of units, donor gender and pregnancies, storage age of red cells and platelets
	
Respiratory support	Inspired oxygen concentration (FIO_2_)	AUC, mean, median and maximum value during the exposure time of interest
	
	Ventilator tidal volumes (mL/kg predicted weight)	AUC, mean, median and maximum value during the exposure time of interest
	Peak and plateau airway pressures (cm H_2_O)	AUC, mean, median and maximum value during the exposure time of interest
	PEEP (cm H_2_O)	5-10 (reference), <5, >10 cm H_2_O
	
	Respiratory rate	AUC, mean, median and maximum value during the exposure time of interest
Medications	Amiodarone	Cumulative dose during the exposure time of interest
	Chemotherapy	Cumulative dose during the exposure time of interest
Other complications	Aspiration (in hospital)	Inhalation of food or gastric contents
	Medical or surgical misadventures	List complication (ICD-9 code E870-E879.9)
**B. Additional biologically plausible hospital exposures - exploratory analysis**		

**Mechanism**	**Variable**	**Measurements**
Inflammation	Corticosteroids, inhaled and systemic	Cumulative dose during the exposure time
	Statins	Cumulative dose during the exposure time
	Insulin	Cumulative dose during the exposure time
	ACE inhibitor	Cumulative dose during the exposure time
Oxidative stress	Antioxidants: *N*-Acetylcysteine, vitamin C, Vit E, Ω 3 fatty acids	Cumulative dose during the exposure time
Coagulation	Anticoagulants (heparin, coumadin)	Cumulative dose during the exposure time
	Antiplatelet agents (aspirin, clopidogrel)	Cumulative dose during the exposure time
Aspiration	Head of the bed position	Above horizontal
	Gastric tube feeding	Cumulative dose during the exposure time
	Sedative agents	Cumulative dose during the exposure time
	Narcotics	Cumulative dose during the exposure time
	Antipsychotics	Cumulative dose during the exposure time
	Gastric acid agents (H_2 _blockers, PPIs)	Cumulative dose during the exposure time
Metabolic	IV fluid (saline, Ringer, albumin)	Cumulative dose during the exposure time
	Furosemide	Cumulative dose during the exposure time
	Beta agonists, inhaled and systemic	Cumulative dose during the exposure time
	Laboratory findings: albumin, pH, glucose, osmolarity	The worst value during the exposure time of interest

AUC - area under the curve, PEEP - positive end expiratory pressure

PPI - proton pump inhibitor

### Bio specimen collection and storage for collaborative genomic and biomarker studies

Having identified both a robust phenotype and a detailed account of potentially important environmental exposures we will collect time sensitive peripheral blood samples for collaborative genome-wide association and plasma biomarker studies. Waste blood samples collected for routine clinical care will be collected at baseline (hospital admission), after 24 and 48 hours, and on the day of development of ALI (if outside these 3 time points).

### Attributable burden of ALI

To prioritize future ALI prevention strategies, we are planning to determine the attributable burden of ALI in the Olmsted County community by quantifying patient-centered outcomes attributable to this condition. The essential patient-centered outcomes (unadjusted and quality-adjusted survival, neurocognitive, neuropsychologic and neuromuscular complications, functional outcome, and quality of life) will be compared between patients who do and do not develop ALI. The instruments we have chosen to evaluate our patients are listed in Table 4. These instruments were selected to assess the key domains of patient centered outcomes without jeopardizing the ability and willingness of the patients to provide data. Specifically these instruments will give a general measure of Quality of life (QOL) (SF12), along with measures of physical, cognitive and psychological functioning and would provide a comprehensive picture of our patients' experience. Baseline (premorbid) functional status and QOL will be determined by in-hospital retrospective survey of the patients or their surrogates. After obtaining informed consent trained study coordinators establish if the patient is competent to complete the entire questionnaire by administering the mini mental test. If patient is deemed incompetent or too ill to complete the survey a surrogate will be identified to help fill the questionnaires. Follow-up contact information will be obtained and the patients or their surrogate who successfully complete the baseline survey will be contacted by telephone six month after index hospitalization.

**Table 4 T4:** Patient-reported outcome assessment.

Variable	Instrument	Time(s) of assessment
Quality of life	SF-12 health survey	1. In hospital retrospective assessment of pre morbid QOL 2. 6 month follow up
Physical function	Barthel Index	1. In hospital retrospective assessment of pre morbid QOL 2. 6 month follow up
Neuromuscular complications	Overall neuropathy limitations scale	1. In hospital retrospective assessment of pre morbid QOL 2. 6 month follow up
Neurocognitive complications	Folstein mini-mental status scale	1. In hospital retrospective assessment of pre morbid QOL 2. 6 month follow up
Neuropsychological complications	1. Post-Traumatic Stress Syndrome (PTSS-10) (only at 6 months) 2. Yale depression scale	1. In hospital retrospective assessment of pre morbid QOL 2. 6 month follow up

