### Strategies for subject retention

We selected survey instruments to minimize respondent burden. In preliminary testing, respondents completed the battery of tests in less than 15 minutes. At baseline the research assistant administer the questionnaire with the use of visual aids to help with answering the questions. When obtaining the consent, patients will be informed of the follow up survey and the same research assistant will contact the patients at six months. This will help in establishing a rapport and increasing the response rate at follow-up. The average retention rate for the surveys conducted by the QOL research team at our institution is in excess of 80%.

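### Table 4 schedules the mini-mental scale as a retrospective premorbid baseline, but it tests present state, is the in-hospital competence screen and cannot be taken by a surrogate

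*Protocol article*

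**What the plan says.** All places are in the protocol article.

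- **Attributable burden of ALI, text.** The premorbid baseline is described for function and quality of life: "Baseline (premorbid) functional status and QOL will be determined by in-hospital retrospective survey of the patients or their surrogates". After consent, coordinators "establish if the patient is competent to complete the entire questionnaire by administering the mini mental test". The surrogate rule follows: "If patient is deemed incompetent or too ill to complete the survey a surrogate will be identified to help fill the questionnaires". At follow-up, "the patients or their surrogate who successfully complete the baseline survey will be contacted by telephone six month after index hospitalization".
- **Table 4.** The neurocognitive row names the "Folstein mini-mental status scale" and times it as "In hospital retrospective assessment of pre morbid QOL 2. 6 month follow up". The other rows carry the same timing. Within the neuropsychological row, the PTSS-10 is marked as a six-month measure only.
- **Strategies for subject retention.** On the mode of the first assessment: "At baseline the research assistant administer the questionnaire with the use of visual aids to help with answering the questions".
- **Statistical Analysis.** Quality of life is compared between ALI patients and controls, allowing for the correlation between baseline and follow-up values. Respondent type is not mentioned.
- **Sample size considerations.** With 100 ALI survivors, 100 controls and an SD of 10 units, the study is said to have 80% power for a 4.0-unit difference in self-reported quality of life.

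**The concern.** The text and Table 4 give one in-hospital score two meanings. In the text it describes the patient's mental state on the day, during acute illness, and decides who answers the survey. In Table 4 it stands for cognition before the illness. An acutely ill patient's score says little about premorbid cognition, and the patients for whom a surrogate is called in are those who cannot complete the survey.

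Neurocognitive complications are among the outcomes that the plan calls essential, and attributable burden is one of the three aims in the Conclusion. If the in-hospital score were used as the baseline, improvement after acute illness would be mixed with any lasting effect of ALI. No later analysis can recover a premorbid measure that was not collected.

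A second, weaker strand concerns the questionnaires. Surrogate help is triggered by illness and by the mini-mental result, so respondent type depends on severity and on one of the outcome instruments.

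**Working it through.** **1. The cognitive measure: the places side by side**

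| Feature | In hospital | Six months |
|---|---|---|
| Use in the text | Screen of present competence | Not stated separately |
| Use in Table 4 | Retrospective premorbid value | Outcome |
| Mode | In person, visual aids | "contacted by telephone six month after index hospitalization" |
| Respondent | Patient, or surrogate if incompetent or too ill | Patient or surrogate |

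- *Backward scoring.* A questionnaire can ask how things were before admission. A performance test cannot, because its score exists only for the time it is taken. The in-hospital column therefore contradicts itself for this scale.
- *Surrogate.* A surrogate can report a patient's function or quality of life. A surrogate who answers mini-mental items is scored on the surrogate's own cognition.
- *Mode.* The two scores would be taken in different ways, and the article names no telephone form of the scale.
- *Is it only a generic label?* The timing text is the same in every row. But Table 4 does exempt the PTSS-10 from the baseline, so instruments without a premorbid value were singled out, and the mini-mental scale was not.

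No arithmetic applies here. The article gives no sample size or target difference for the scale.

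**2. The quality-of-life figure in the plan**

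Inputs from Sample size considerations: 100 per group, SD 10, difference 4.0, power 80%. Two-sided alpha of 0.05 is assumed for this endpoint; the article gives 0.05 for the case-control power figure.

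- SE = 10 × √(2/100) = 1.41.
- Power = Φ(4.0/1.41 − 1.96) = 80.7%.
- n for 80% power = 2 × (1.96 + 0.84)² × 10²/4.0², rounded up to 99 per group.

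The plan's figure reproduces. There is no arithmetic error.

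**3. What surrogate response could do to that comparison**

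Bias in a six-month group difference = (difference between groups in surrogate share) × (mean surrogate-minus-patient shift). The documents give neither input, so both are assumptions: a share difference of 10 to 40 percentage points and a shift of 2 to 10 units.

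| Share difference | Shift (units) | Bias (units) | Share of 4.0 | False-positive rate | Power if bias opposes a true 4.0 |
|---|---|---|---|---|---|
| 0.10 | 2 | 0.2 | 5% | 0.052 | 77% |
| 0.20 | 5 | 1.0 | 25% | 0.11 | 56% |
| 0.40 | 10 | 4.0 | 100% | 0.81 | 3% |

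False-positive rate = Φ(bias/SE − 1.96) + Φ(−bias/SE − 1.96). Power uses 4.0 − bias as the effective difference.

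If the same type of respondent answers at both times and the shift is constant, it enters baseline and follow-up equally. The bias in change is then (share difference × shift) − (share difference × shift) = 0. The range therefore runs from nothing to the whole target difference, and the documents do not say where in it this study would fall.

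**The case against.** **The strongest reply is that no cognitive change analysis is written.** The sentence on the retrospective baseline covers function and quality of life, the serial-correlation sentence covers quality of life, and cognition is only said to be compared between groups. A six-month comparison does not need the in-hospital score. This stands, and it limits the point to any baseline or change built on the scale as Table 4 schedules it. It does not remove the contradiction in Table 4.

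**A reader might infer that surrogates answer mainly for ALI patients.** The article does not say so. The rule is per patient and applies equally to controls, who are matched on age, gender and predicted ALI risk. Surrogates help fill in the forms and need not replace the patient. Higher use in ALI cases is plausible, because the Background notes that ALI is often the reason for ICU admission, but it remains an inference.

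**A reader might also infer a false recovery that is larger in ALI patients.** The article does not place the baseline survey before or after ALI onset, so a differential depression of the in-hospital score cannot be shown.

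**The respondent may already be held constant.** The follow-up sentence can be read as re-contacting whoever completed the baseline. A constant shift would then largely cancel in change.

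**Some details may sit in documents not shown.** A telephone form of the instrument and a covariate for respondent type are commonly left to a full protocol or analysis plan. Their absence here is no fault in itself. Cognitive screening by telephone is feasible, so the telephone contact does not rule out a six-month cognitive outcome.

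**Conclusion.** The point holds for the cognitive measure. As scheduled in Table 4, the mini-mental scale cannot supply a premorbid baseline or be answered by a surrogate, and its two administrations differ in mode. A cognitive baseline or change score formed from it would be invalid. This follows from the text alone and needs no assumption about numbers.

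For the SF-12 and the other questionnaires, the finding is a risk only. Surrogate response depends on illness and sits badly with a power statement for self-reported quality of life, so it may bias the comparison. The range of 0.2 to 4.0 units rests wholly on assumed shares and shifts, and the direction is open. The documents do not support a statement that the quality-of-life comparison is biased, or biased against one group.

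The primary endpoint (development of ALI) and unadjusted survival are not affected.

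**What to change.** 1. Keep the in-hospital mini-mental test as the competence screen only, and remove it from Table 4 as a premorbid measure.
2. At six months, compare groups on a cognitive score taken from the patient, not a surrogate, with an instrument suited to the telephone. Name the instrument in Table 4.
3. If premorbid cognition is wanted, obtain it from a short informant questionnaire and adjust the six-month comparison for it.
4. For the SF-12 and the other questionnaires, record respondent type (patient, patient with surrogate help, surrogate) at both times. Repeat the comparison in patients with the same respondent type at both, and align the self-reported wording in Sample size considerations with the surrogate rule.

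Cost: a change to Table 4 and a small form change, best made before data collection because premorbid status cannot be reconstructed later. The in-hospital mini-mental score is no longer a baseline outcome, and patients who cannot be tested at six months have no cognitive score. The same-respondent analysis will also be smaller. If, as an assumption, 80 per group remained, SE = 10 × √(2/80) = 1.58 and power for 4.0 units would be Φ(4.0/1.58 − 1.96) = 72%. It should therefore be read as a sensitivity analysis.
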